## Methods

The design is a four-arm, parallel RCT designed to investigate the effectiveness of combined cognitive and physical training versus cognitive and physical training alone but combined with a control activity, in comparison to an active control group, to promote cognitive and neurofunctional improvements in older adults. Fig. 1 shows the Consolidated Standards of Reporting Trials flow diagram corresponding to the present study.

**Fig. 1 Fig1:**
[figure not shown]
Flow chart of the study protocol. d/wk days per week.

### Study design

Participants will complete one of the four combinations of cognitive training with video games and physical exercise. The cognitive component will be either a brain-training video-game program selected from Lumosity (cognitive intervention, CI) or video games not specifically designed to train particular cognitive functions such as attention, memory, or executive control (cognitive control, CC). The physical exercise component will be either a senior-friendly adaption of BODYATTACK™ (https://www.lesmills.com/), a combination of dance, aerobic, strength, and muscular resistance (exercise intervention, EI), or its control condition comprising stretching, toning, and relaxation (exercise control, EC). The duration of sessions for all groups will be the same, and all participants will perform physical exercise and video-gaming activities in a social environment (in small groups formed by 10–12 participants) and in the presence of the trainer.

To summarize, the study will have a 4 × 3 mixed factorial design with four intervention conditions—multidomain (CI + EI), uni-domain cognitive intervention (CI + EC), uni-domain physical intervention (EI + CC), and active control (CC + EC)—assessed at three different time points (pretest, posttest, 3-month follow-up), with “Type of training” as between-subject factors and “Time” as the within-subject factor. The dependent variables will be behavioral and/or electrophysiological measures of executive functions (inhibition, shifting, working memory), memory functions (short term and long-term visual and word memory), and emotional well-being, quality of life, and motivation.

### Trial setting

This study will be conducted in Madrid (Spain) at the UNED Psychology building. The screening, pretest, posttest, and follow-up assessments will be conducted in our laboratories at the Psychology building. The training sessions of the four groups will be conducted in three waves in spaces specifically equipped and prepared for this purpose at our university site as well as at a city council facility.

### Participants

Participants will be male and female, healthy, and independently living volunteers aged between 60 and 80 years. Those who complete the baseline assessments and meet the inclusion criteria (see later) will be randomly assigned to one of the four intervention conditions. The timing of group allocation will take place between 1 and 8 weeks after baseline.

Participants may discontinue their intervention for personal or medical reasons. To minimize dropouts and improve adherence to the intervention, four face-to-face adherence reminder sessions will take place during the training program emphasizing the importance of training compliance. Furthermore, to increase participant retention and to reduce loss to follow-up, all participants will receive a personalized report of their performance and training progress at the end of the study. Participants will receive a small refund in compensation for their travelling expenses.

Even though this trial is low risk, participants might harm themselves during the practice of physical exercise. To minimize the risk of injuries, each participant will be carefully monitored during the training sessions. The interventions will be designed in collaboration with the exercise instructors, after a detailed analysis and taking into account each participant’s possible medical issues. Spontaneously reported adverse events or other unintended effects will be registered and analyzed, and if necessary the protocol will be modified to eliminate the causing element. We have signed an insurance policy in case any participant suffers harm during the physical training.

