In this RCT, we will use questionnaire data to verify that the groups do not differ in their levels of intrinsic motivation and engagement. At the end of the assessment session, participants will report their expectations regarding their performance in the assessment tasks using a 5-point Likert scale. Moreover, at the 1st, 8th, and 16th training session, the participants will respond to questions about motivation and engagement for each of the training video games. These factors will be examined by comparing the intervention arms to the active control condition. The engagement and motivation data will be used in secondary analyses as covariates in order to rule out these factors as sources of variation in the primary outcome variables.

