### Outcome measures

Each group will be assessed at three time points. Possible improvement will be assessed at posttest (12 weeks) and follow-up (24 weeks) using baseline (week 0) outcomes as a reference point. A schematic diagram of the time schedule of data collection for all outcome measures is shown in Fig. 2 (see also Additional file 1: SPIRIT checklist).

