##### The 6-Minute Walk Test (6MWT)

The 6MWT [104] is commonly used to assess exercise capacity. The participant walks for 6 min as fast as possible. The primary outcome is the distance completed. The test is administered in accordance with the protocol endorsed by the ATS [105]. The test is performed on a straight 30-m corridor and all participants receive standardized scripted instructions and scripted phrases of encouragement each minute during the test. Besides the distance, monitored parameters are changes in oxygen saturation (SpO_2_), and pretest and posttest dyspnea and fatigue using the Borg scale [106].

Functional capacity is assessed in the study with the 6MWT. The outcome measure will be the mean absolute value in the test obtained by the groups at three time points: pretest, posttest, and follow-up. The specific metric will be the mean change from pretest to the other time points of the study.

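### Adverse events are registered from spontaneous reports and no solicited harms question is described, so delayed or between-session harm depends on being volunteered; one neutral question at existing contacts should be added

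*Protocol article*

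**What the plan says.** The harms arrangements are in the Participants section of the protocol article. It calls the trial low risk but accepts that people may be injured while exercising. Three safeguards follow:

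- Observation in class: "each participant will be carefully monitored during the training sessions".
- Design: the interventions are worked out with the exercise instructors, with each participant's possible medical issues in mind.
- Registration and response: "Spontaneously reported adverse events or other unintended effects will be registered and analyzed, and if necessary the protocol will be modified". The purpose of the modification is stated too: "the protocol will be modified to eliminate the causing element".

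The same section schedules four face-to-face sessions during training, described as adherence reminders.

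Other sections bear on the point:

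- Objectives and hypotheses schedules a questionnaire during training: "at the 1st, 8th, and 16th training session, the participants will respond to questions about motivation and engagement".
- The 6-Minute Walk Test section records "pretest and posttest dyspnea and fatigue using the Borg scale".
- Trial setting states: "The training sessions of the four groups will be conducted in three waves".
- Study design describes the active exercise as a "senior-friendly adaption of BODYATTACK".
- Physical intervention sets the intensity at 65–80% of maximum heart rate and includes plyometric movements.

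**The concern.** The plan makes the corrective step depend on registered events, and it names spontaneous reports as how adverse events come to be registered. A harm that nobody sees and the participant does not mention cannot trigger that step.

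An injury in class is likely to be seen. Pain that builds up at home between sessions is not visible in the same way. It is a foreseeable type of harm here: participants are 60 to 80 years old, are selected for little or no exercise habit, and in the two exercise-intervention arms train twice a week at moderate to high intensity.

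Because training runs in three waves, an element that causes such harm could stay in the regimen for the rest of a wave and be carried into later ones. At stake are participant safety and the completeness of the harms data. The cognitive outcomes and their analysis are not involved.

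**Working it through.** The article states no figure for harms, so there is nothing to reproduce. The check is a reading of every place where harms could be asked about, followed by a count of the contacts available.

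**Step 1. What each contact or body is described as doing**

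| Place in the article | Stated purpose | Would it pick up unvolunteered harm between sessions? |
|---|---|---|
| In-class monitoring (Participants) | Reduce injury risk during training | Only if visible in class |
| Four adherence reminder sessions (Participants) | Stress compliance | An occasion to volunteer it; no harms question described |
| Sessions 1, 8 and 16 (Objectives and hypotheses) | Motivation and engagement with the games | No |
| Borg ratings and oxygen saturation (6-Minute Walk Test) | State around the walk test | No; they do not ask about events since the last contact |
| Data monitoring committee | Correct collection, encoding and storage of data | No harms review described |
| Steering committee | Compliance, timelines and trial processes | No harms review described |
| Schedule figure (Outcome measures) | Timing of assessments | Unknown; the figure is not shown |

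The abbreviation list under the schedule figure names no harms instrument, but a row in plain words would not appear there. The finding is therefore limited to the visible text.

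**Step 2. Whether the size can be stated**

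Let n be the participants exposed, r the risk of a between-session harm and s the share volunteered. Expected recorded events = n × r × s.

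- From the Sample size section: n = 2 × 36 = 72 in the two exercise-intervention arms.
- Not in the article: r and s.

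As an illustration of direction only, assume r = 5%. Then 72 × 0.05 = 3.6 harms are expected. With s assumed at 30%, 50% or 70%, the expected number recorded is 1.1, 1.8 or 2.5. Recorded events fall in proportion to s, and any size of loss follows from the choice of r and s. Asking would raise s by an unknown amount and not necessarily to 100%. No figure for the gain is claimed.

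**Step 3. What asking would cost**

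- Contacts that already take place: 16 sessions + posttest + follow-up = 18.
- Most answers possible: 144 × 18 = 2,592.
- At an assumed one minute each: 2,592 / 60 = 43.2 hours over the whole trial.

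**The case against.** The best case for the plan is that passive reporting with close supervision is proportionate in a low-risk trial of healthy volunteers. Musculoskeletal conditions and significant heart or lung disease are excluded, and the exercise is adapted for older people. Participants meet a trainer twice a week in groups of 10–12 and have four further face-to-face sessions. Pain bad enough to call for a change would often show as limited movement, absence or withdrawal for medical reasons. This stands, and it confines the gap to delayed harm that is neither mentioned nor visible.

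A second argument is that a condensed article may leave harms forms to the full protocol. This stands in part. A missing form would be no finding. Here, however, the article itself names the method of capture and makes the corrective action depend on its yield.

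Stronger readings are tempting but unsupported:

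- A reader might infer that spontaneous reports are the sole channel. The text does not say so. It also registers other unintended effects without restricting their source, which may include what trainers see.
- A reader might infer that harms are captured unequally between the exercise intervention and the exercise control. That is possible, but nothing in the article shows it.
- A reader might want a probability that a wave's harms go unregistered. It would rest wholly on assumed rates, and comparing it with near-zero loss after the change would assume perfect disclosure. Since the protocol is modified only where necessary, one unrecorded minor ache also does not mean that a harmful element was kept.

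**Conclusion.** The point holds as an optional, minor safety improvement. The article names spontaneous reporting as the source of registered adverse events, ties modification of the regimen to registered events, and describes no solicited harms question in the visible text. Delayed or between-session harm therefore depends on being volunteered, while acute or severe harm is likely to come to light by other routes.

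The size of the gain cannot be stated from the document. The conclusion assumes that the unseen schedule figure contains no harms question; if it does, the point falls away. The efficacy analysis is unaffected either way.

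**What to change.** Keep spontaneous and trainer-observed reporting, and **add** one neutral question, worded identically and asked of every participant in all four arms at each of the 16 training sessions, at posttest (12 weeks) and at follow-up (24 weeks). For example: *Since we last saw you, have you had any new pain, injury or other health problem?*

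- Do not replace spontaneous reporting. It is still needed between contacts, in the roughly 12 weeks between posttest and follow-up, and for people who stop attending, who could be asked only at posttest and follow-up if they come.
- Record solicited and spontaneous events separately.
- Recruitment began in February 2019 and the trial is described as ongoing. If a wave has already started, record the date the question was introduced, so that earlier and later event counts are not read as like for like.
- Apply the existing rule on modifying the protocol to all recorded events, whatever their source.

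The cost is at most 2,592 one-line answers, about 43 hours in total at the assumed minute each, and less if the question is a line on an attendance sheet. The main downside is that more minor background complaints will be recorded. No visit, outcome or sample size changes.

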### Inclusion and exclusion criteria

Participants will have normal or corrected to normal vision and hearing, and will be free of neurological or musculoskeletal conditions, psychiatric conditions, or traumatic brain damage. They will not practice intense sports or other forms of physical exercise and will not play video games of any sort for more than 1 h per week. To determine eligibility, participants will be screened individually. Exclusion criteria will be a score of below 26 on the Mini-Mental State Examination (MMSE) [77], a score of 6 or more on the Yesavage Geriatric Depression Scale [78] (Spanish adaptation by Martínez et al. [79]), less than 20/60 vision with or without correction based on self-report, inability to complete the training activities, inability to communicate in Spanish, current plans to move to another city, and significant heart or lung disease.

### Sample size

We conducted an a priori power analysis using G*Power 3.1 [80] to calculate the appropriate sample size. Using an α value of 0.05, power of 0.80, and a medium effect size (*f* = 0.38) for video-game training [45] and physical training [81], and four groups within the *F*-test family, a total sample size of 124 is required. Considering a dropout rate of 12%, a total of 144 participants would be sufficient to detect significant main effects. According to this calculation, the adequate number of participants in each group (multidomain training, video-game training, physical activity training, and active control) is 36. According to this, we will set a sample size of 36 participants per arm, which is adequate for the experimental design. According to Montgomery et al. [82], with this number of participants the design would be underpowered to detect an interaction effect, as it would need a fourfold increase in sample size. However, given that lower interaction effects would not be clinically relevant, we decided to maintain our initial sample size estimation.

In the elaboration of this protocol, we have followed the SPIRIT 2013 explanation and elaboration guidance for reporting protocols of clinical trials [83].

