Cognitive training is an intervention that allows structured training in a series of tasks relevant to different cognitive functions, such as executive functions, speed of processing, episodic memory, cognitive control, or attention. Among cognitive psychologists and neuroscientists there is increasing interest in exploring whether cognitive training with specially designed computerized training programs and video games of different kinds enhances cognition. Video games are electronic games that require interaction with a computer or other electronic devices with a user interface that provides visual and auditory feedback. Computerized cognitive programs and video games are currently receiving great attention in exploring the possibility of transfer to untrained tasks [37–42]. Many intervention studies based on cognitive training support the idea that training in older adults improves some aspects of cognition but not others. In recent years, several meta-analyses [43–47] have examined the effectiveness of computer-based interventions in healthy older adults. These meta-analytic studies have shown low to moderate training effects in older adults in several cognitive processes that decline with age, such as processing speed, attention, and memory. However, others [48] have reported that playing video games had little consequences on cognition. Due to different study designs (e.g., the inclusion of active or passive control groups [49, 50]) and types of training (e.g., video games of different kinds, computerized cognitive programs [51–54]), results have been heterogeneous, making it difficult to reach solid conclusions [55].

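### The stated inputs (alpha 0.05, power 0.80, f = 0.38, four groups) give N = 80, not 124; with f = 0.38, 124 has about 95% power

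*Protocol article*

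**What the plan says.** All of this is in the protocol article, Methods, Sample size.

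- Software: "We conducted an a priori power analysis using G*Power 3.1".
- Inputs: "Using an α value of 0.05, power of 0.80, and a medium effect size", with the value f = 0.38 given in brackets and two literature sources cited for it, one on video-game training and one on physical training.
- Test: "four groups within the" F-test family. The particular test, its numerator degrees of freedom, the number of measurements and their correlation are not given.
- Result: "a total sample size of 124 is required".
- Dropout: "Considering a dropout rate of 12%, a total of 144 participants would be sufficient to detect significant main effects".
- Allocation: "we will set a sample size of 36 participants per arm".

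The same paragraph concedes that an interaction would be underpowered. The calculation is offered for main effects only.

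**The concern.** This is the only power statement in the article, and it gives enough inputs to be checked. Alpha, power, effect size and number of groups fix the sample size of a four-group omnibus F test, and the result is well below 124. A gap of 44 participants (124 − 80) is too large for rounding.

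What is at stake is the accuracy of the trial's stated justification. A reader who takes the paragraph at face value will believe that 124 evaluable participants give 80% power at f = 0.38. They give clearly more, or the effect detectable at 80% power is clearly smaller than 0.38. The word medium beside the value adds a second, smaller difficulty, because 0.38 is not what most readers understand by a medium f.

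**Working it through.** **Inputs, all from the Sample size section:** alpha = 0.05; power = 0.80; f = 0.38; k = 4 equal groups; dropout 12%.

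**Method.** One-way omnibus F test with the noncentral F distribution: df1 = k − 1 = 3, df2 = N − 4, noncentrality λ = N·f². With f = 0.38, f² = 0.1444. Power is the probability that a noncentral F(3, N − 4, λ) exceeds the 5% critical value.

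**Step 1. Attempt to reproduce 124 at 80% power.**

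| N | per arm | λ = 0.1444·N | critical F | power |
|---|---|---|---|---|
| 76 | 19 | 10.97 | 2.73 | 0.779 |
| 80 | 20 | 11.55 | 2.72 | 0.803 |
| 120 | 30 | 17.33 | 2.68 | 0.945 |
| 124 | 31 | 17.91 | 2.68 | 0.952 |
| 144 | 36 | 20.79 | 2.67 | 0.976 |

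The smallest balanced N for 80% power is 80. The stated 124 is not reproduced. It is, however, exactly the smallest balanced N for 95% power (120 falls short at 0.945).

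**Step 2. Effect size that 124 detects at 80% power.** Solving for f with N = 124 and power 0.80 gives f = 0.301 (λ = 124 × 0.3014² = 11.26).

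**Step 3. Could another F test give 124 at 80% power?** The test is not named, so alternatives were tried with f = 0.38.

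- One numerator degree of freedom: 57.
- ANCOVA with one covariate: 80.
- Repeated-measures between-groups test, three measurements: 32 to 80 for correlations from 0 to 0.99.
- Within-between interaction, three measurements: the answer depends on the noncentrality convention and the sphericity correction ε. With λ = N·f²·m·ε/(1 − ρ), where m is the number of measurements and ρ their correlation, it is at most 56. With λ = N·f²·ε it is 100 (ε = 1), 120 (ε = 0.75) or 156 (ε = 0.5).
- Alpha divided by 6: 120.

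None gives exactly 124 at 80% power. Those that come near it need inputs that the article does not state.

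**Step 4. Dropout.** 124 / (1 − 0.12) = 140.9, so 141, and 144 when rounded up to four equal arms of 36. This step is sound. The fault lies only in the combination of 0.80, 0.38 and 124.

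**Step 5. The label.** The usual convention for f is 0.25 medium and 0.40 large. The article does not give it, so it enters here as an assumption. On that scale 0.38 is close to large. At f = 0.25 and N = 124, λ = 7.75 and power is 0.623; 80% power would need N = 180 (power 0.804).

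**The case against.** The strongest reply is that the error does no harm to the design. The section's conclusion is that 144 participants suffice for main effects, and on its own f = 0.38 that is true with room to spare: 0.95 power with 124 and 0.98 with 144. Recruitment, allocation and analysis stay as they are. This stands, and it limits the point to a wrong statement of power.

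A second reply is that the F test is not named, so an unstated option might have produced 124. This stands in part. Repeated-measures answers do vary with convention, and the 95% setting is an inference from an exact match, not something that the article shows. But no option tried gives 124 at 80% power from the stated inputs.

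A third reply is that the value 0.38 is printed beside the word medium and that the label does not enter the calculation. This also stands, so the label is a secondary matter.

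Two stronger readings are tempting, and the article supports neither.

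- A reader might infer that the trial is underpowered and that the mismatch would lead to null results being over-interpreted. The mismatch understates power at f = 0.38, so it cannot do that by itself. Such harm would need a true effect smaller than 0.38, which is a separate claim.
- A reader might infer that 0.38 is a standardised mean difference entered as f, because the Background says of a group of meta-analyses that includes the cited video-game source: "These meta-analytic studies have shown low to moderate training effects in older adults". That sentence gives no metric and no value for the source. The physical-training source also cited for 0.38 is not in that group. Neither source is available here, so no power figure should be built on this idea.

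**Conclusion.** The point holds as an internal inconsistency in the power statement. For a four-group omnibus F test at alpha 0.05 and f = 0.38, 80% power needs 80 participants, and 124 give 95.2%. If 80% power is kept with 124, the detectable effect is f of about 0.30. One of the three figures must be wrong; a power setting of 0.95 is the likeliest explanation but is unconfirmed.

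The size of the error is 44 participants, or about 15 percentage points of power, in the conservative direction. The sample size is not too small for the stated main effect.

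This rests on reading the four-group F test as a one-way omnibus test with equal arms, which is the reading closest to the inputs given. The remark on the medium label rests on a convention from outside the document, and the main conclusion does not depend on it.

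**What to change.** Keep 144 participants (36 per arm) and the dropout step. In the Sample size section:

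1. Name the F test that was run, with its numerator degrees of freedom and, if it was a repeated-measures test, the number of measurements, the correlation and the sphericity correction.
2. Restate the result along these lines: 124 evaluable participants give about 95% power for f = 0.38, or 80% power for f of about 0.30. If the named test turns out to be a different one, give the figures for that test.
3. Drop the word medium, or keep it and add that power at f = 0.25 with 124 participants is about 62%.

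The cost is one reworded paragraph and one re-run of the power calculation. No participants are added, and the design and analysis do not change.
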